##### Classification of hospitalizations during the following year

For all included patients, the re-hospitalizations in medicine or surgery departments that took place during the year of follow-up will be identified from the SNDS base and classified into three categories: 1) readmission for management of recurrence and post-stroke complications; 2) readjustment for post-stroke follow-up and secondary prevention of stroke and 3) re-hospitalizations to manage a clinical situation not related to stroke.

This classification will be carried out in three stages: 1) automated classification based on ICD-10 codes and procedures associated with readmission, 2) for re-hospitalizations not classifiable in an automated way, the IRC will return to the corresponding patient record, within the hospitalization facility and 3) if it is impossible for IRC to classify rehospitalization, a group of experts (including 3 neurologists and a rehabilitation doctor) will meet to classify each remaining hospitalization, based on the information from the hospitalization report.

##### Procedure for searching for lost-of-follow-up

During follow-ups at 3 months and 1 year, if the patient is unreachable, the IRC will contact the treating physician and / or the person around the patient to identify a change in the patient’s place of life or death.

In addition, once all the SNDS links have been completed, the data manager will identify deaths during a hospitalization of unreachable patients during follow-ups at 3 months and 1 year.

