#### Patient selection criteria

The inclusion criteria into the PAPASéPA cohort are: inclusion criteria to ObA2 (being over 18 years of age living in metropolitan France, suffering from a recent stroke whose diagnosis was confirmed by a neuro-vascular physician) and as additional criteria, Giving consent to participate to PAPASéPA).

Patients will be identified prospectively as they are included in ObA2. The inclusions will be carried out continuously and prospectively from the date of the beginning of inclusions (planned to be in september 2019) until the required number of subjects is obtained in each strata.

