The extraction from the ObA2 database will provide information about patient socio-demographic characteristics (date of birth, sex, place of residence), clinical (medical history, risk factors, medical treatment before hospital, type of stroke) and acute phase pathways (pre-hospital: date/time start of symptoms, date/time call to general practitioner, date/time call to emergency medical services, place of occurrence of the stroke, mode of transport, date/time of admission to hospital; hospital stay: initial stroke management, complementary investigations, in-hospital complications, hospital rehabilitation and medico-social care; at discharge: NIHSS, medical treatment at discharge, patient referral) (Table 1).

The National Health Data System regroups healthcare reimbursement data from in-patient and outpatient care, as well as causes of death. It provides data on claims paid for each patient by the French National Social Security System and is therefore the main source of information on healthcare costs. This database contains patient data (age, sex, place of living, long-term and chronic diseases, date of birth, date of death, health insurance scheme, benefit of free complementary insurance for lower-income people), all consultations and visits to General Practitioners (GPs) and ambulatory care specialists (but nothing about their content), all medical technical procedures, all dispensed medical devices and drugs, all lab and diagnostics tests but not their results, and providers’ level data (their activity and sales turnover, geography, prescribing behaviour). In addition, mortality and cause of death data are also available in this database.

Extractions from the SNDS will cover the time period from September 2019 to August 2020 and provide information about the post-stroke care pathway (Table 1):

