◦ Number / type / duration of hospitalization in medicine or surgery departments, rehabilitation department, psychiatry department and hospitalization at home. Hospitalisations will be classified into three categories corresponding to hospital stays with different clinical meanings with regard to the evolution of stroke (readmission for management of stroke recurrence and post-stroke complications, readjustment for post-stroke follow-up and secondary prevention of stroke and re-hospitalizations to manage a clinical situation not related to stroke);◦ Number / type of medical and paramedical consultations at hospital;◦ Medical ambulatory care: number / type of medical consultations (general practitioner, neurologist, functional rehabilitation physician, cardiologist) and of paramedical consultations (physiotherapy, speech therapy, orthopsy), number of care periods, total duration of each care period;◦ Quantity of drug deliveries (antiaggregant, antihypertensive, statin or anticoagulant treatment, analgesic);◦ Vital status of patients.

**Ad hoc collection** at any of three points in the study (initial episode, at 3 months and 1 year after the initial episode).

The collection time for each variable is specified in Table 1. The categories of variables collected are as follows:
◦ **Clinical data:** risk factors (Alcohol), severity of stroke at discharge (NIHSS)◦ **Stroke life pathways data:** patient referral, level of education, marital status, cohabitation status, professional activity, ability to drive, place of life, participation to a therapeutic education program, medical and social care, allowances for disability, presence of family and caregiver, development and technique to improve autonomy and home care, technical assistance for walking, legal background.◦ **Post-stroke sequelae assessment**

A selection of scales measuring each of the dimensions explored in our project was selected, based on elements of feasibility, frequency of use in the exploration of the dimension considered and metrological performance (validity and reproducibility): The mode of collection of sequelae has been adapted according to the validated mode of administration for each of the scales. The following sequelae are assessed:

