**Cog impairment** using the **French Telephone Interview for Cognitive Status Modified (F-TICS-m).** The TICS scale is a tool for screening for memory disorders. It evaluates time orientation, spatial orientation, immediate memory, calculation, semantic memory, delayed recall, language, understanding of an instruction. Cut offs of 24 and 34 are used (a score less than 24 corresponds to dementia, a score between 24 and 33 corresponds to mild cognitive impairment and a score more than 34 corresponds to a normal condition). This scale was validated in French by telephone [19].**Depression and anxiety** using the **hospital anxiety and depression scale (HADS)**. The anxiety and depression score through the HADS seeks to identify an anxiety-depressive symptomatology and assess its severity. It is composed of 14 items divided into 2 scores of seven items each: a depression score (one for dysphoria, one for deceleration and five for the anhedonic dimension) and an anxiety score. Each item is rated from 0 to 3, allowing to obtain 2 scores. The maximum score for each score is 21. This scale was validated in French by telephone and in a self-administered collection mode [20].**Fatigue** using the **Fatigue Severity Scale (FSS).** The fatigue score through the FSS measures the impact of fatigue on different functions. This is a short questionnaire of nine questions, to which the patient answers on a scale from 1 to 7. The overall score is the average of all the scores obtained on each of the 9 questions. The higher the result, the greater the fatigue. A threshold of 5.5 is often used to differentiate high and low fatigue. This scale was validated in French in a self-administered collection mode [21].**Genito-sexual disorders** using closed-ended question “yes/no”.**Limitations of activities** using the **modified Rankin Scale (mRS)** [23] and the **Barthel Index (BI)** [22]. The modified Rankin Scale (mRS) and the Barthel Index (BI) are commonly used scales measuring the actual abilities of the stroke patient in the basic activities that determine autonomy. The mRS is a more global scale, which measures functional independence rather than the performance of specific tasks. In this way, mental as well as physical adaptations following neurological deficits are assessed. The scale consists of 7 levels, from 0 to 6, with 0 corresponding to no symptoms and 6 corresponding to death. Cut offs of 2 is used (a score less than or equal to 2 corresponds to independence, a score greater than 2 corresponds to dependence). This scale was validated in French by telephone and in self or hetero-administered data collection mode. The IB was developed in 1965 [22] and later modified by Granger and colleagues [43] to measure patient performance in 10 activities of daily living. The IB is considered a sensitive and reliable disability scale for stroke patients. The IB items can be divided into two groups: one, related to self-care (diet, grooming, bathing, clothing, urinary and anal continence, and toilet use) and the other, related to mobility (ambulation, transfers and stair climbing). The maximum score is 100, which indicates that the patient is totally independent in physical functioning. The lowest score is 0, which represents a totally dependent bedridden state. A dependency to consider a return home is usually defined by a score greater than or equal to 60. The IB is a scale validated in French in a data collection mode by interview (hetero-administered).**Participation restrictions** using the **Community Integration Questionnaire (CIQ)**. The CIQ assesses disability for brainy people in three areas: home integration (active participation in the functioning of the home or household), social integration (participation in social activities outside the home), productivity (regular work performance). It is composed of three sub-scores: home integration [0–12], social integration [0–10], productivity [0–7]. The total CIQ score [0–29] is the sum of the 3 sub-scores.

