#### Statistical analysis

##### Analysis strategy

The analysis of the assessment criteria will be carried out on available data, i.e. without any replacement of missing data. For the analysis of the primary endpoint, a sensitivity analysis of missing data, using a multiple imputation method, may be considered. The analysis will be carried out using the SAS 9.3 software (or later version) considering a risk of first species fixed at α = 5%. A statistical analysis plan will be defined blind data.

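### For unreachable patients the SNDS search covers only in-hospital deaths, so an out-of-hospital death that nobody reports would be missing instead of mRS 6

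*Protocol article*

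**What the plan says.** The section *Procedure for searching for lost-of-follow-up* gives two routes for a patient who cannot be reached at 3 months or 1 year.

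- Enquiry: "the IRC will contact the treating physician and / or the person around the patient to identify a change in the patient’s place of life or". The sentence then closes by naming the patient's death as the other thing to find out. No place of death is specified.
- Linkage: once the SNDS links are complete, "the data manager will identify deaths during a hospitalization of unreachable patients during follow-ups at 3 months and 1 year".

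*Data sources* describes the SNDS more broadly. Date of death is among its patient-level data, and the article adds: "In addition, mortality and cause of death data are also available in this database". The list of items to extract ends with "Vital status of patients", with no restriction to hospital deaths or to unreachable patients. The same section fixes the window: "Extractions from the SNDS will cover the time period from September 2019 to August 2020". Under *Patient selection criteria*, inclusion is planned to start in September 2019 and runs "until the required number of subjects is obtained in each strata".

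*Evaluation criteria* makes death a separate category of the primary endpoint at both time points. *Sample size selection* assumes 19% deaths and 5 to 10% lost to follow-up. *Analysis strategy* states: "The analysis of the assessment criteria will be carried out on available data, i.e. without any replacement of missing data". A multiple-imputation sensitivity analysis is mentioned only as a possibility.

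**The concern.** The linkage rule is narrower than the data it draws on. For an unreachable patient, whether linkage finds a death depends on whether the patient was in hospital when it happened. Place of life and hospital stays are among the pathway components under study, so outcome ascertainment may be tied to exposure.

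Two results are at stake. One is the frequency of death, since *Expected outcomes* promises precise outcome frequencies. The other is the set of odds ratios for pathway components, if deaths are missed more often at one level of a component than at another. Imputation is a weak remedy, because it would guess the state of a patient whose death may already be recorded in the linked database.

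**Working it through.** **1. The plan's own figure.** Inputs from *Sample size selection*: 51% / 30% / 19%, odds ratio 2, exposure 20% or 80%, 5% (two-sided assumed), 80% power. The proportional-odds formula is N = 3(z_α+z_β)² / [e(1−e)(ln OR)²(1−Σp³)]. Here Σp³ = 0.133 + 0.027 + 0.007 = 0.167, and N = 3 × 7.849 / (0.16 × 0.4805 × 0.8335) = 367.5, so 368. Then 3 × 368 = 1104. The planned 1210 corresponds to a loss of 1 − 1104/1210 = 8.8%, within the stated 5–10%. The sample size is sound and is not affected by this point.

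**2. Deaths at stake.** Expected deaths: 0.19 × 1210 = 229.9. This applies the 19% to the whole cohort; the article does not say which time point it refers to.

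**3. Deaths missed (illustrative).** Neither share below is in the documents. Assume 30–60% of deaths occur outside hospital and 10–30% of those are reported by neither physician nor relatives.

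- Low: 229.9 × 0.30 × 0.10 = 6.9, or 3% of deaths. Observed share (229.9 − 6.9)/(1210 − 6.9) = 18.5%.
- High: 229.9 × 0.60 × 0.30 = 41.4, or 18% of deaths. Observed share (229.9 − 41.4)/(1210 − 41.4) = 16.1%.

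These shares suppose that nobody else is lost.

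**4. Upper bound if survivors are lost too.** Let l be the proportion lost and d the proportion of the lost who died, with no death recovered. Missed deaths = 1210 × l × d; observed share = (0.19 − l·d)/(1 − l).

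| l | d | Missed deaths | Observed share |
|---|---|---|---|
| 5% | 19% | 11.5 | 19.0% |
| 5% | 50% | 30.2 | 17.4% |
| 10% | 19% | 23.0 | 19.0% |
| 10% | 50% | 60.5 | 15.6% |

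The share is biased only if the lost die more often than the rest. Because both routes recover some deaths, the counts are ceilings.

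**5. Effect on the odds ratio.** A proportional-odds model was refitted to expected counts with a true odds ratio of 2, the plan's marginal distribution, and exposure of 20%, 50% and 80%. All loss patterns are assumed (order: independent / dependent / dead).

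- 0/15/25% lost in both exposure groups: odds ratio 1.99–2.00; death share 0.1425/0.9075 = 15.7%.
- 0/15/25% in the exposed, flat 5% in the unexposed: about 1.61–1.62.
- 0/15/25% in the unexposed, flat 5% in the exposed: about 2.46–2.48.
- Deaths only, 25% missed in the unexposed and none in the exposed: 2.36 (20% exposed) to 2.245 (80% exposed).

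The first three patterns also drop survivors, so they show the mechanism and do not measure this rule alone.

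**6. The extraction window.** It spans 12 months and opens in the month inclusion starts, so only patients with a stroke at the very start of September 2019 can have a full year in it. *Representativeness of cohort* gives 5230 strokes in the 13 centres in 2016. Even if every patient were included at that rate, 1210 inclusions take 1210/5230 × 12 = 2.8 months, to late November 2019. The last one-year date then falls in late November 2020, about three months after the window closes. Filling three severity strata can only lengthen this.

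**The case against.** The strongest reply is that the deaths are already covered. The nurse's enquiry has no limit on place of death, the linkage step is an addition to it, and vital status is a listed SNDS item for all patients. Nothing says a known death would be ignored when mRS 6 is assigned. Much of this stands: the protocol is partly inconsistent with itself, and no absence of data is shown. It does not remove the point, because the one sentence that says what is done for unreachable patients names hospital deaths only.

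A reader might infer that out-of-hospital deaths in general, and dependent survivors as a class, drop out of the primary endpoint. The documents do not support that. Deaths reported by the physician or relatives are captured wherever they occur. Asking for a new place of life may well allow renewed contact, although the text does not say so. Any survivor who stays unreachable is missing, whether independent or dependent.

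A reader might also infer that home or institutional care would look safer than it is. No passage fixes that direction, and step 5 shows the odds ratio can move either way or hardly at all.

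It is tempting, too, to call the lack of a proxy mRS an error, because of the mRS the article says: "This scale was validated in French by telephone and in self or hetero-administered data collection mode". But for the Barthel Index the same section explains hetero-administered as by interview, so this does not show validated rating by a relative in the patient's absence. *Main outcome* is already concerned with reproducibility and limits rating to three trained people. Proxy rating is an optional trade-off and not part of this point.

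Finally, the model uses both time points with a random effect, so a patient seen at 3 months still contributes. That helps, but it does not supply a death that was never recorded.

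**Conclusion.** The point holds in a limited form. The stated linkage rule for unreachable patients is narrower than the data the protocol plans to extract. An out-of-hospital death that neither physician nor relatives report would count as missing instead of mRS 6 in the available-data primary analysis.

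Deaths would be undercounted. The death share is understated if the patients lost die more often than those followed. Odds ratios are materially biased only if ascertainment also differs by pathway component. Neither size nor direction can be determined from the documents: 7 to 41 missed deaths rests on two assumed ranges, 11 to 61 is a ceiling under other assumptions, and the odds ratios in step 5 rest on assumed loss patterns. The extraction window is a separate, firm problem, because as written it cannot give one-year vital status for most patients.

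**What to change.** - Reword *Procedure for searching for lost-of-follow-up* so that SNDS vital status and date of death, for any place of death, are used for all included patients. Applying the rule to everyone keeps ascertainment independent of reachability.
- Set mRS = 6 at 3 months and at 1 year when the date of death falls on or before that time point, counted from the stroke.
- In *Data sources*, replace the fixed September 2019 to August 2020 window with one that runs to the last included patient's one-year date.

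The first two are wording changes, since the variable is already on the extraction list. The real cost is a later or longer SNDS extraction. The article does not say whether the data-protection authorisation under *Ethics* covers a longer window, so that should be checked. The sample size does not change.

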### Evaluation criteria

The main evaluation criteria is post-stroke activity limitations by the mRS grouped into three categories ([0; 2]: independence;[3; 5]: dependence; 6: death), at 3 months and 1 year after the acute episode.

The secondary evaluation criteria are:

Other post-stroke sequelae at 3 months and 1 year
◦ Post-stroke cognitive disorders by TICS score grouped into 3 categories (24: dementia; [24; 33]: MCI; 34: normal) at 3 months and 1 year after the acute episode.◦ Post-stroke anxiety and depression disorders by HADS score according to 2 sub-score of anxiety and depression, each grouped into 3 categories ([0; 7]: absence of cases; [8; 10]: questionable state; [11; 21]: certain state) at 3 months and 1 year after the acute episode.◦ Post-stroke fatigue by the FSS score grouped into 2 categories (5.5: low fatigue; 5.5: high fatigue) at 3 months and 1 year after the acute episode.

Post-stroke activity limitations by BI grouped into 4 categories (< 20: bedridden; [20–59]: partial autonomy; [60–79]: autonomy for return home; 80: complete autonomy) at 3 months and 1 year after the acute episode. Restrictions on post-stroke participation by the CIQ-R score grouped into 4 categories ([0–12]: home integration; [0–10]: social integration; [0–7]: productivity; [0–6]: electronic social networking) at 3 months and 1 year after the acute episode. Patient clusters responding to pathways with common or similar characteristics (pathway typology).

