### Data management and statistical analysis

#### Sample size selection

The primary endpoint is the mRS, measured at 3 months and 1 year after the stroke. Based on data from a pilot study, we assume a prevalence of independence of 51%, dependence of 30% and death of 19%. Several simulations were performed by varying the frequency of exposure to the risk factor studied (very rare to very common). By fixing the risk of first species at 5% and the power of the association test at 80%, to show an odds ratio of at least 2 (odds ratios to move to a higher class: independence to dependence or death, dependence on death), 368 patients should be included to cover a change in exposure to the risk factor studied, ranging from 20% (rare exposure) to 80% (frequent exposure).

The study is stratified on the NIHSS score assessed at inclusion (at the end of the hospital stay for acute episode management) in 3 categories (≤6, 7–16, > 16) and needs to include 368 patients per category of NIHSS or 1104 patients in total (software R v3.3.1).

To account for an estimated 5 to 10% of lost to follow-up, it is necessary to include 1210 patients.

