##### Analysis plan

Characteristics of patients at inclusion and during the study.

Patients will be described to the following variables: compliance with eligibility criteria; socio-demographic, clinical, and pathways characteristics. A description of the violations of the protocol, causes of death and abandonment will be made and patients who have died, lost sight of, or abandoned research may be described and compared with other patients.

Analysis of the primary endpoint.

The mRS, the primary endpoint, is an ordered variable with three response modalities. The analysis is based on a Proportional Odds Model, assuming an identical odds ratio for each possible dichotomization of the criterion.

In order to take into account the correlation between the measurement of the mRS at 3 months and that one at 1 year, a random effect on the time will be systematically added to the models.

The odds proportionality hypothesis and the log-linearity hypothesis will be systematically checked.

Analysis of secondary endpoints
◦ Typology of the different patient stroke pathways

In order to identify the types of paths, a hierarchical clustering, or latent class clustering, will be carried out.
◦ Stroke elements associated with post-stroke sequelae

In order to evaluate the association between the pathway elements and each of the identified sequelae, linear, logistic or polytomic regression models with random effects will be implemented. The assumptions underlying the modelling used will be systematically verified.
◦ Social and geographical inequalities in care

The social and geographical characteristics of the patients included will be described and compared, using the descriptive and comparative statistical methods detailed above, between the different types of pathways identified.

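### The fatigue and HADS endpoints are defined as two or three classes although the full scores are collected; this costs the association analyses information, and the listed linear model is not tied to any endpoint

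*Protocol article*

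**What the plan says.** All references are to the protocol article.

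- **Scores collected.** Under Data sources, the FSS is the mean of nine items, each rated 1 to 7. The HADS gives two sub-scores, each the sum of seven items rated 0 to 3, so each runs from 0 to 21.
- **Endpoint form.** Evaluation criteria then list "Post-stroke fatigue by the FSS score grouped into 2 categories", with 5.5 as the dividing value, and "Post-stroke anxiety and depression disorders by HADS score according to 2 sub-score of anxiety and depression, each grouped into 3 categories" (0–7, 8–10 and 11–21).
- **Reason for the cut.** For the FSS, Data sources say only this: "A threshold of 5.5 is often used to differentiate high and low fatigue". The HADS classes carry clinical labels (no case, questionable, certain). No reason is given for testing associations on classes rather than on the score.
- **Use of the endpoints.** Under Objectives, the first secondary objective is to identify pathway components associated with sequelae other than activity limitation, including fatigue and anxiety-depression, at 3 months and 1 year.
- **Model.** For these associations the Analysis plan says "linear, logistic or polytomic regression models with random effects will be implemented". It does not say which model goes with which endpoint.

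**The concern.** A score with many levels is collected, then reduced to two or three levels before it is used to look for associations. Patients on the same side of a cut are treated as identical, and patients just either side of it as different. For describing how common a problem is, that is acceptable. For detecting an association it wastes information that is already in the database.

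The list of models does not settle the matter. A linear model does not suit a two- or three-class endpoint, so a statistician who follows Evaluation criteria literally will use a logistic or polytomous model on the classes. One who follows the Analysis plan could use a linear model on the score. The two readings give different analyses of the same objective.

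What is at stake is the sensitivity of the fatigue and mood part of that objective. These scales exist only for survivors and come back by post, so the number analysed will already be below the cohort size.

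**Working it through.** **The plan's own figure.** The only sample size is for the three-category mRS, in Sample size selection: "we assume a prevalence of independence of 51%, dependence of 30% and death of 19" per cent, 5% type I error, 80% power, "to show an odds ratio of at least 2", exposure 20% to 80%. The proportional-odds formula of Whitehead, with two-sided α, is

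N = 3(z₁₋α/₂ + z₁₋β)² / [e(1−e)(ln OR)²(1 − Σpᵢ³)].

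Here Σpᵢ³ = 0.51³ + 0.30³ + 0.19³ = 0.1665 and e(1−e) = 0.16, so N = 3 × 2.8016² / (0.16 × 0.4805 × 0.8335) = 367.5, rounded up to 368. The stated 368 per stratum is reproduced, and 3 × 368 = 1104. This concerns the mRS only; nothing in it gives power for the FSS or HADS.

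**Efficiency of a grouped score.** For a normal score and a small shift, the share of information kept by ordered classes with proportions pᵢ and cut points cᵢ is

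E = Σ [φ(cᵢ₋₁) − φ(cᵢ)]² / pᵢ, where φ is the standard normal density.

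For two classes this reduces to φ(c)² / [p(1−p)]. The class proportions below are assumptions, because the article gives none. The last column is the power left when the full score would have 80%: Φ(2.8016·√E − 1.96).

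*FSS, two classes*

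| Share with high fatigue | φ(c) | E | Loss | Power if 80% on full score |
|---|---|---|---|---|
| 50% | 0.3989 | 0.637 | 36% | 61% |
| 40% | 0.3863 | 0.622 | 38% | 60% |
| 30% | 0.3477 | 0.576 | 42% | 57% |
| 20% | 0.2800 | 0.490 | 51% | 50% |

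The 50% row is the best that any single cut can do, so 36% is a floor under these assumptions. Below 20% the loss grows: 57% at 15% high and 66% at 10%.

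*HADS, three ordered classes*

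| Split (0–7 / 8–10 / 11–21) | E | Loss | Power if 80% on full score |
|---|---|---|---|
| equal thirds | 0.793 | 21% | 70% |
| 50/25/25 | 0.749 | 25% | 68% |
| 60/20/20 | 0.697 | 30% | 65% |
| 65/20/15 | 0.668 | 33% | 63% |
| 75/15/10 | 0.578 | 42% | 57% |
| 80/12/8 | 0.518 | 48% | 52% |

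Worked line for 60/20/20: cuts at 0.2533 and 0.8416, densities 0.3863 and 0.2800, so E = 0.3863²/0.6 + (0.3863 − 0.2800)²/0.2 + 0.2800²/0.2 = 0.249 + 0.057 + 0.392 = 0.697.

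**What this means at the planned size.** The loss in power points depends on the effect and on whether the NIHSS strata are pooled. Take an odds ratio of 2 for high fatigue and survivors at 81% of 1104, which is 894 (298 per stratum). The approximate test statistic is ln 2 × √[N·e(1−e)·p(1−p)]; dividing it by √E gives the full-score value.

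- Pooled, 70% postal return assumed (N = 626), 20% exposed, 20% high fatigue: 0.693 × √(626 × 0.16 × 0.16) = 2.77, power 79%. Full score: 2.77/0.70 = 3.96, power 98%. Loss about 18 points.
- Pooled, full return (N = 894), 50% exposed, 50% high fatigue: 0.693 × √(894/16) = 5.18, power 99.9%. Loss near zero.
- One stratum, full return (N = 298), 20% exposed, 20% high fatigue: 0.693 × √(298 × 0.0256) = 1.91, power 48%. Full score: 2.73, power 78%. Loss about 30 points.

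The loss of information is therefore stable, but the loss of power is not.

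**The case against.** The strongest defence has four parts.

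1. **The form of analysis is not firmly fixed.** Linear models are listed, and the Analysis strategy section promises an analysis plan that is not at hand. Assigning models to secondary endpoints is commonly left there. This stands in part: a full-score analysis is not excluded. But the grouped form is stated in Evaluation criteria, so it is not simply left open, and the unassigned list does not override it. The linear option may also have been meant for the CIQ-R sub-scores.
2. **The classes are conventional and readable.** Odds of a clinically labelled state match the odds-ratio format of the primary endpoint and suit a study meant to inform care planning. This is a fair reason to report the classes, not to base the search for associations on them alone.
3. **The starting power of 80% is not the article's figure for these endpoints.** This stands fully. If strata are pooled and the effect is large, the cost in power can be negligible.
4. **Normality is assumed for bounded scores.** This also stands; skewness or a ceiling would change the percentages.

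Three stronger readings are tempting and are not supported. A reader might infer that both scales lose a third to a half of their information; that fits the FSS over the range shown, but HADS can lose as little as about a fifth. A reader might infer that true associations will probably be reported as absent; powers of 50% to 68% do not imply that. A reader might take the polytomous model to be nominal and so to ignore the order of the HADS classes; the article never says nominal, and it uses a proportional odds model for its ordered primary endpoint.

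**Conclusion.** The point holds as a worthwhile improvement to a secondary objective, not as an error that invalidates a stated result. Evaluation criteria reduce collected scores to classes, the Analysis plan does not say whether the classes or the scores enter the association models, and following the endpoint definitions as written gives up information for no stated reason.

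Under a roughly normal score, small effects and assumed splits, the loss is at least 36% for the FSS (36–51% with 20–50% high fatigue) and about 20–45% for the HADS sub-scores analysed as ordered. The illustrative fall from 80% power is to about 50–61% for the FSS, and to about 57–68% for HADS (splits from 50/25/25 to 75/15/10). The actual fall cannot be fixed from the article, because it states no power, effect size or prevalence for these endpoints and does not say whether the strata are pooled for them.

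**What to change.** In Evaluation criteria, name the FSS mean score and the two HADS sub-scores as the endpoints for the association analyses. Keep the 5.5 cut and the 0–7, 8–10 and 11–21 classes for describing how frequent these sequelae are. In the Analysis plan, assign the model: a random-effects linear model on the score, or a random-effects cumulative-logit model if the score is skewed or piled up at a bound. Make both changes before the data are examined; the Analysis strategy section already foresees an analysis plan defined on blind data.

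The cost is wording and model choice only. The full scores are already collected, linear random-effects models are already listed, and the primary analysis already uses a proportional odds model. The downside is that effects become score differences or cumulative odds ratios instead of odds of being a case, so the class frequencies should be shown beside them.
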